#### Long-term outcomes

This randomised trial is designed to estimate the effects of a tailored digital intervention on alcohol consumption and its consequences in the short term. The long-term outcomes of digital interventions are, however, understudied.^78^ Therefore, to study the long-term outcomes of a potential dissemination of the intervention, we will simulate outcomes using an agent-based model.^79^ The agent-based model will be parameterised using data from national registries regarding population statistics, including incidence of disease and mortality, as well as findings from epidemiological studies concerning the relative risk of disease attributed to alcohol consumption. This will provide estimates of the expected reduction in the number of incident cases of alcohol-related diseases, including cancers and liver diseases, which a dissemination of the intervention could result in. Additionally, the gains from dissemination in terms of increased population-wide quality-adjusted life years and reduced healthcare and societal costs can be estimated using this method.

#### Exploratory analyses

In the effectiveness trial of the personalised intervention, we used a waiting list control group to contrast outcomes. Waiting lists are known to introduce biases in research,^80 81^ and in this trial, we are blinding participants and placing individuals on a waiting list without their knowledge (control group participants will be offered an evidence-based intervention once trial participation is complete). To estimate the bias introduced by using a waiting list in the previous trial, we will create a four-way contrast using the personalised intervention group and control group in the current study with both groups of the previous study using the same analytical methods as proposed here for primary outcomes, including analyses of attrition, mediation and heterogeneity of effects. Although groups will not be concurrent, it will nevertheless give an estimation of the bias induced by study design choices.

We will explore inter-relationships between sets of outcomes, for instance, comparing the AUDIT-C data with primary outcomes, and alcohol-related consequences with alcohol consumption and quality of life. We will also explore how readiness to change and motives change over time in the enhanced tailored group.

### Patient and public involvement

There was no direct patient and public involvement in the development of the interventions or the design of the trial.

## Ethics and dissemination

The success of the personalised digital interventions in reducing alcohol consumption highlights that providing support for alcohol consumption via digital means is effective.^16^ However, questions remain about whether the digital format can yield enhanced effects through attention to how the intervention can be tailored to individual needs. The current study is an evaluation of whether tailoring the intervention with respect to an individual’s motives for drinking and their readiness to change has a greater impact on alcohol consumption compared with both a previously studied intervention and support materials available online. Tailoring content in the manner attempted here could result in a more nuanced intervention that improves on our capacity to support behaviour change.

The study received ethical approval from the Swedish Ethical Review Authority (16 April 2024, Dnr 2024-01630-01). A complete data set is expected to be available by October 2026, at which time analyses will be conducted. We plan to disseminate findings from the trial through open-access peer-reviewed journals and conferences in 2027. Deviations from the protocol will be reported when findings are published.

### Limitations

This trial will have minimal barriers to participation and, therefore, we anticipate that follow-up attrition will be a major limitation. To reduce attrition as much as possible, we will use a follow-up routine involving reminder texts and phone calls, which we have successfully used before.^16 71 82^ The Bayesian sequential design we use in this trial will ensure that we keep recruiting participants until we have satisfied the recruitment criteria, thus preserving precision in our statistical estimates. However, this does not protect against attrition bias stemming from systematic missingness. We have planned to study attrition in our ancillary analyses and use multiple imputations to see how findings are sensitive to missing data.

We will attempt to keep participants blind throughout the trial. The study is advertised as one that evaluates digital support, but neither the advertisement nor the informed consent materials provide details about the nature of the support. This blinding is likely to be successful for the two intervention groups. However, controls will be given material they have likely come across online before, which may make them realise that they are, in fact, controls. We will nevertheless attempt to blind controls in this study to attend to a limitation of the previously conducted trial of the personalised version of the digital intervention.^16 20^ That trial used a waiting list group as a control, which may induce bias due to research participation effects.^8083^,^85^ The decision to use this procedure also presents an ethical risk, as those who sign up seeking help to reduce their drinking will be asked to use online resources that do not comprise proven effective intervention materials. To partially mitigate the risk, we will make the personalised intervention available to controls once they have completed their trial participation.

We use outcome measures related to alcohol consumption as primary in this trial as the interventions are designed to reduce alcohol consumption. However, for some individuals, for instance those with coping motives, it may be more relevant to focus more on reduced alcohol-related problems and less on consumption. We acknowledge that this trial will be limited in its ability to discover these nuances.

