### Statistical methods

All analyses will be done keeping participants in the groups to which they were randomised (intention-to-treat). In addition to three-way contrasts, analyses will also be conducted contrasting the two intervention groups combined versus the control group.

Analyses will be done using both available data and imputation. Imputation will be done using multiple imputation with chained equations (generating 200 data sets using predictive mean matching).^73^ Bayesian inference will be used to estimate the parameters of the models.^74^ Inference will be carried out using Stan, and convergence will be reported using trace plots, R-hat statistics and effective sample sizes. For each coefficient of interest, we will report the marginal posterior probability of effect, and the median will be used as a point estimate of the magnitude of the effect. We will also report 95% compatibility intervals defined by the posterior distributions’ 2.5% and 97.5% percentiles.

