#### Models for primary and secondary outcomes

Primary outcomes will be modelled using multilevel regression with participant-level adaptive intercepts and group-by-time interactions (2-month, 4-month and 8-month follow-up measures). Secondary outcomes are measured at 8 months only and will be analysed using regression models with a group covariate. Both primary alcohol consumption outcomes will be modelled using negative binomial regression, and so will the number of visits to emergency healthcare services. Logistic regression will be used for hazardous and risky alcohol consumption classification, and linear regression will be used for the combined consumption measure (AUDIT-C), alcohol-related consequences scores (SIP) and quality of life (PROMIS Global Health 1.2). Frequency of drinking, typical number of drinks consumed on a drinking day and alcohol-related injury will be modelled using ordinal regression. Models of primary outcomes will be adjusted for baseline measures of the outcome using a time-by-baseline interaction, and models of secondary outcomes will be adjusted for baseline measures of both primary outcomes. In addition, all models will be adjusted for age, sex, education and access to money on short notice (see online supplemental Appendix A). We will use Student’s t priors for the main intercepts and coefficients, and half-Student’s t priors for dispersion and error terms. All Student’s t priors will be centred at 0, have a scale of 2.5 and 3 df. We will use normal priors for adaptive intercepts with standard normal hyperpriors for the SD parameters (mean=0, SD=1).

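### For the primary outcomes, comparing available-data and imputed results does not test departures from missing at random, although the Limitations section offers imputation as part of its answer to systematic missingness

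*Protocol article*

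**What the plan says.** Under Limitations, the article states "we anticipate that follow-up attrition will be a major limitation". It adds that continued recruitment preserves precision but that "this does not protect against attrition bias stemming from systematic missingness". The response follows at once, in one sentence with two parts: the ancillary attrition analyses, and a plan to "use multiple imputations to see how findings are sensitive to missing data".

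Statistical methods sets out the two analysis sets: "Analyses will be done using both available data and imputation". The imputation is "multiple imputation with chained equations (generating 200 data sets using predictive mean matching"), and no not-at-random departure is stated.

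Models for primary and secondary outcomes gives the model that is fitted to the available data: "Primary outcomes will be modelled using multilevel regression with participant-level adaptive intercepts and group-by-time interactions". It is a negative binomial model over 2, 4 and 8 months, adjusted for the baseline outcome and four covariates.

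Ancillary analyses adds two attrition analyses. The first regresses the primary outcomes on the number of contact attempts needed, reasoning that late responders may resemble non-responders. The second is a logistic model of response on baseline variables with group interactions.

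**The concern.** A multilevel likelihood (or Bayesian) model fitted to available repeated measures is valid when missingness depends only on data that are observed and modelled. Standard chained-equation imputation needs the same kind of condition. Predictive mean matching fills each gap with a value borrowed from an observed participant who has a similar prediction. If non-responders drink more than their observed history predicts, neither analysis sees it.

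The risk is one of interpretation. Similar results from the two analyses could be reported as robustness to attrition when the threat named in the Limitations section has not been tested. This matters most for the enhanced versus personalised contrast at 4 months. That contrast drives the recruitment criteria, and the article uses a 15% relative difference both as the simulated effect and as the futility margin.

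**Working it through.** **The plan's own figure.** The only related figure is the anticipated 1750-2200 participants (Sample size). It cannot be rebuilt from the article, because the outcome mean, dispersion and attrition inputs are not in the text. The point does not depend on it.

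**Inputs.** IRR 0.85 is the 15% difference simulated under Sample size. The 95% posterior probability threshold is the benefit criterion in the same section. The share missing, m, is not given, so 30-40% is assumed for the main cases and 20-50% for the tipping range.

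**Step 1: effect of a departure on the IRR.** Let d1 and d2 be the ratios of true to imputed mean drinking among non-responders in the enhanced and personalised arms. Assume equal m in both arms and an imputed mean equal to the responders' mean within each arm. Then

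factor = [(1 - m) + m·d1] / [(1 - m) + m·d2]

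| d1, d2 | m = 0.30 | m = 0.40 |
|---|---|---|
| 1.25, 1.00 | 1.075; 0.85 becomes 0.914 | 1.10; 0.85 becomes 0.935 |
| 1.50, 1.00 | 1.15; 0.85 becomes 0.978 | 1.20; 0.85 becomes 1.02 |
| 1.25, 1.10 | 1.075/1.03 = 1.044; 0.85 becomes 0.887 | 1.10/1.04 = 1.058; 0.85 becomes 0.899 |
| equal | 1.00; unchanged | 1.00; unchanged |

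**Step 2: multiplier that brings 0.85 to 1.00, enhanced arm only.** k = 1 + (1/0.85 - 1)/m = 1 + 0.1765/m. This gives 1.88, 1.59, 1.44 and 1.35 at m = 0.20, 0.30, 0.40 and 0.50.

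**Step 3: effect on the benefit criterion.** Suppose 0.85 only just reaches 95% posterior probability, with a normal approximation on the log scale. The posterior SD is then 0.1625/1.645 = 0.099. At 0.914 the probability is Φ(0.090/0.099), about 82%. At 0.935 it is Φ(0.067/0.099), about 75%.

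**Step 4: do the two planned analyses reveal such a departure?** One illustrative simulation used two arms of 6000, a true IRR of 1.00, negative binomial counts at three follow-ups and a random intercept. The model was fitted by maximum likelihood with baseline-by-time adjustment, and imputation used predictive mean matching with 8 data sets. All settings are assumptions. Results at 4 months:

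| Dropout depends on | Missing by arm | Full data | Available data | Imputed |
|---|---|---|---|---|
| observed data | 34%, 36% | 0.975 | 0.966 | 0.975 |
| unseen current outcome, more strongly in the intervention arm | 33%, 38% | 1.015 | 0.885 | 0.884 |

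In the second row both analyses show the same spurious reduction of about 12% and differ by 0.001.

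**Step 5: does a delta-adjusted imputation show it?** In the second scenario, multiplying imputed intervention-arm counts by 1.25, 1.5 and 2.0 moved the 4-month IRR from 0.884 to 0.964, 1.043 and 1.173. The Step 1 formula with m = 0.38 predicts 0.884 × 1.095 = 0.968 for the first and 0.884 × 1.19 = 1.052 for the second, close to the fitted values.

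**The case against.** The strongest reply is that the Limitations sentence names two measures, and that the contact-attempts regression is the one aimed at systematic missingness. That stands. A reader might infer that imputation is the plan's only check, or that not-at-random missingness was overlooked; the documents support neither. What remains is that the attempts analysis, as described, relates outcomes to attempts and does not re-estimate the group effect.

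Second, a reader might infer that the two analyses rest on an identical assumption everywhere and must agree by construction. That is too strong. The article does not list the imputation predictors, and these could include the other primary outcome and the mediators. For secondary outcomes, "Secondary outcomes are measured at 8 months only and will be analysed using regression models with a group covariate", so imputation could use the 2- and 4-month data that those regressions leave out, and there the comparison can be informative. Systematic missingness that observed data explain is within the reach of imputation. None of this extends to dropout that depends on the unseen outcome.

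Third, a delta analysis may sit in an analysis plan that is not shown, so its absence from an article is not a fault in itself. Agreed. The point is about what the article says imputation will show.

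Fourth, the larger shifts need a departure in one arm only. The two active arms follow the same logic, share one follow-up routine and are expected to stay blinded, so a strong one-arm departure is less plausible there than against controls. That is fair, and bringing 0.85 to 1.00 needs a sizeable multiplier. Some differential remains conceivable: the enhanced arm has periodic reassessment questionnaires, and the article's own response model allows group interactions.

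**Conclusion.** The point holds for the two primary outcomes. Comparing available-data with imputed results tests sensitivity to how observed information is used, not to departures from missing at random, and no analysis described gives a group effect under such a departure.

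With 30-40% assumed missing, a 25% departure in the enhanced arm only takes 0.85 to 0.91-0.94. A result that only just met the benefit criterion would fall to about 82% or 75% posterior probability. Full reversal to 1.00 needs a multiplier of 1.59 (30% missing) or 1.44 (40% missing) in that arm alone, and equal departures change nothing. These sizes rest on the assumed attrition, equal missingness by arm and the simple mean-scale formula.

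A reader might go further and conclude that the trial's estimates will be biased or that the analysis is invalid. The documents do not show that: they give neither an attrition rate nor evidence of differential departure. The plan should be amended, but its main analysis stands.

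**What to change.** 1. Keep the available-data and imputed analyses, and label both as missing-at-random analyses.
2. Add a delta-adjusted (pattern-mixture) imputation for both primary outcomes at 4 and 8 months. Multiply imputed counts by a prespecified set of factors, for example 1.0, 1.1, 1.25 and 1.5. Apply them first in all arms, then in the enhanced arm only, and in both intervention arms for the contrast with controls. This grid is one reasonable choice among several.
3. Use the late-responder results from the contact-attempts analysis, by arm, to inform the range. This carries the article's own reasoning through to the effect estimate.
4. Report the multiplier at which the posterior probability of benefit falls below 95%, extending the grid if it is not reached.
5. Reword the Limitations sentence to say that the available-data versus imputation comparison does not address not-at-random missingness, and that the attrition and delta-adjusted analyses do.

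The cost is analysis-plan wording and computing time, with no new data. The article expects the complete data set by October 2026, so the analysis can be fixed before then. The drawback is that a published tipping point may make the result look less firm.
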